### Ethics

According to the Helsinki Declaration protocol (1964) [56], written informed consent will be obtained from the participants. All participants receive a signed copy. Each participant will receive a unique coded alphanumeric identification ensuring data anonymity in accordance with the General Data Protection Regulation (GDPR), following Regulation (EU) 2016/679 of the European Parliament of April 27, 2016, and the Personal Data Protection Law, according to Law No. 58/2019 of August 8. The files that connect alphanumeric codes to participants identifying information will be stored in a separate locked file protected by a password access system, only known by the principal investigator [48].

This study will be based on the ethical standards required in scientific research and was submitted for review by the Ethics Committee of the Polytechnic University of Leiria and approved on March 27, 2024 (reference: CE/IPLEIRIA/47/2024). Study procedures, protocol risks voluntary character of participation and expected results will be explained to the participants. The right to withdraw without any prejudice or consequence will be ensured.

### Intervention

The intervention will take place over 8 weeks at the Municipal Pool of Paião, located in Figueira da Foz, Portugal. The AG will conduct the aquatic exercise program, while the ALG will carry out both aquatic and land-based exercise programs. The intervention will begin after a one-week washout period, during which participants will cease any additional physical exercise, which they will maintain throughout the intervention weeks.

To monitor the intensity of the interventions, Borg CR-10 scale will be used. This is a tool to rate dyspnea and/or perceived exertion (RPE) experienced by an individual. The scale consists of a numerical list with 10 points (0–10), an adaptation of the original scale (6–20), that assesses and monitors the intensity/severity of shortness of breath/fatigue. Its use requires explaining that “0" means not experiencing dyspnea/fatigue at the moment and that “10" means the worst dyspnea/fatigue they have ever experienced or the worst imaginable dyspnea/fatigue [57,58]. This instrument will not be used during the assessment moments before and after the exercise programs but only to monitor the intensity during the sessions of both aquatic and land-based exercise programs. This scale is validated for monitoring dyspnea and fatigue, showing an excellent correlation with heart rate (r=0.92) and VO2 (*r*=0.92–0.93) and moderate reliability (ICC=0.50–0.66) [59].

Participants will be encouraged to maintain their daily activities as usual outside of the study. The participants may not participate in any other exercise programs.

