## Abstract

**Background:**

Chronic low back pain (CLBP) is a disease with significant functional, emotional and social impact. Several interventions are proposed for its management and exercise is one of main, land-based or water-based. This study describes a randomized controlled trial that will analyze the effect of a combined aquatic and land-based exercise program compared to an aquatic-based program on pain, functional incapacity and quality of life in adults with CLBP. Additionally, it will analyze the effects of exercise cessation in the same outcomes.

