**Methods and design:**

A blind randomized controlled trial will be developed with a 1:1 allocation ratio. Around 30 adults with mechanical CLBP will be randomly allocated in two groups. The experimental group (ALG) will complete an aquatic and land-based exercise program and control group (AG) will carry out only an aquatic program, both for 8 weeks. Participants will be assessed with Visual Analogue Scale, Oswestry Disability Index, Short-Form 36, Tampa Scale of Kinesiophobia-13 and Modified-Modified Schober Test, collected at baseline (M0), after 8 weeks (M1) and 4 weeks after the end of the intervention (M2).

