Moreover, few authors have investigated the effects of cessation of exercise [45,46]. Mujika & Padilla [46] argue that detraining can be divided into two study periods: short-term, less than 4 weeks, and long-term, more than 4 weeks. Therefore, Toraman & Ayceman [47] found that after 4 weeks of interruption following a 9-week aerobic, strength, and flexibility training program, conducted 3 times a week, participants showed a reduction in performance levels on various functional tests, standing out the Chair Sit and Reach, compared to the end of the intervention, although the changes were not statistically significant. Thus, the impact of aquatic exercise, core stability exercise, and trunk and lower limb stretching cessation on individuals with CLBP remains unclear.

This trial aims to assess the effect of a combined aquatic and land-based exercise program compared to an aquatic program on pain, functional disability, and quality of life in adults with CLBP. Secondary objectives include investigating the effects on lumbar mobility and fear of movement, as well as the impact of training cessation on these variables 4 weeks after the end of the intervention. We hypothesize that combined aquatic and land-based exercise decreases significantly pain, and functional disability, and increases quality of life in adults with CLBP.

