#### Data Collection.

After enrollment, participants will complete three evaluation phases: before the intervention (M0), after the intervention (M1), and 4 weeks after the end of the intervention (M2). Data collection started in November 2024 and is expected to be completed in April 2025. During data collection, participants will start each data collection session by filling out the questionnaires (Oswestry Disability Index, MOS Short Form Health Survey 36 Item, and Tampa Scale of Kinesiophobia-13) and the Visual Analog Scale for pain at rest, during movement, and at night, which will take approximately 30 minutes. Following this, the physiotherapist responsible for the assessment will measure weight and height, and then assess lumbar spine mobility using the Modified-Modified Schober Test, taking the best of three measurements. To standardize data collection, each participant will be asked to stand barefoot on a paper where the outline of their feet will be drawn to ensure consistent positioning across all measurements. This procedure will be repeated three times, with a 30-second break between repetitions. Participants will be instructed to place their feet at hip-width apart and their upper limbs relaxed along the body in the test starting position [68,69]. Fig 2 shows the study design with key moments of the intervention and data collection.

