The study (RCT) with the most similar methodology was conducted with 66 participants (33 in each group) and aimed to examine the effect of an experimental aquatic and land-based exercise program compared to a control program of exclusively land-based (home-based) [43]. After two weeks of intervention, statistically significant differences were observed favoring the experimental intervention in pain: VAS at rest (ρ < 0.001), during exercise (ρ < 0.001), and overall in the lumbar spine (ρ < 0.001); in the ODI score (ρ = 0.045); and in the SF-36 domains of physical performance (ρ = 0.033), mental health (ρ = 0.021), pain (ρ = 0.014), and general health (ρ = 0.05). No statistically significant differences were found between the groups in the remaining domains of the SF-36 questionnaire or in the Modified-Modified Schober Test.

No study with a similar methodology has reported results for the TSK-13 questionnaire to date. Thus, it is challenging to predict the results of the study, as the methodologies differ and the sample sizes and intervention durations vary considerably among authors. It is not possible to project whether the group that will undertake the additional land-based exercise session will achieve better outcomes than the experimental group at the end of the intervention, in the studied variables. However, the variables most sensitive to the presented interventions appear to be pain, measured by VAS, functional disability measured by ODI, and some domains of the SF-36 related to pain and physical performance. These are likely to be the variables with the greatest variability at the end of the study. On the other hand, it is difficult to predict the trend of changes in the studied variables after 1 month of exercise cessation due to the lack of reference literature.

Thus, this study aims to provide implications for the practice and prescription of physical exercise and effective strategies that may contribute to potential benefits for individuals with LBP. Like all studies, this one will have some limitations: it will be impossible to fully control activities outside of the protocol, which may affect the studied variables either positively or negatively, and aquatic exercise limits the calculation of exercise intensity, which will be monitored only through perceived exertion.

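### The cessation objective cannot be answered as an effect of stopping exercise: both arms stop at week 8, the exercise rule for the following 4 weeks is unclear, and the text describes no record of exercise or treatment in them

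*Protocol article*

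**What the plan says.** The Abstract (Background) promises: "Additionally, it will analyze the effects of exercise cessation in the same outcomes". The aims at the end of the Introduction list among the secondary objectives "the impact of training cessation on these variables 4 weeks after the end of the intervention". The opening paragraph of the Discussion repeats the intention in softer terms.

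On the arms, the Abstract (Methods and design) gives the experimental group the combined programme and says that the "control group (AG) will carry out only an aquatic program, both for 8 weeks". Under Data Collection, everyone is assessed before the intervention (M0), after it (M1) and 4 weeks after its end (M2).

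The Intervention section has two rules on other exercise. The first starts with a one-week washout, in which "participants will cease any additional physical exercise, which they will maintain throughout the intervention weeks". The second, at the end of the general part of that section, forbids taking part in exercise programmes outside the trial and names no period.

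Under Data Collection, the measurements listed for each session are the questionnaires, the VAS, weight, height and the lumbar mobility test. Under Participant adherence, attendance at the supervised sessions is logged. The Discussion concedes that "it will be impossible to fully control activities outside of the protocol". Under Statistical analysis, a 2×3 (arm by time) ANOVA is planned.

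**The concern.** An effect of stopping is a contrast between stopping and not stopping. In this design every participant stops at the same time, so nothing shows what the M2 scores would have been had training continued.

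The exposure itself is also not secured. If the dated restriction is the operative one, participants who gave up their own exercise may take it up again in the very weeks meant to represent cessation. This is plausible, because the Introduction itself reports the recommendation that people with this condition stay active. If the undated sentence is the operative one, they may not join a programme, but the text describes no way to verify this.

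The stake is interpretation. A flat course from M1 to M2 could be lasting benefit or resumed exercise. A worsening could be detraining or ordinary fluctuation. Followed as written, the plan would allow either to be reported as an effect of cessation.

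**Working it through.** **1. The plan's own figure.** Inputs from the Participants section: effect size 1.079, α = 0.05, power 80%, 15 per group. A two-sided two-sample t-test (noncentral t) requires n = 14.51, rounded up to 15 per group and 30 in total. Power at 15 per group is 0.814. The stated 30 is reproduced. It was set for a between-group difference in VAS pain, not for cessation.

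**2. What the M1–M2 change contains.** Within one arm,

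mean(M2) − mean(M1) = C + T + N,

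where C is the effect of stopping against continuing, T is the change that would have occurred anyway over those 4 weeks, and N is the effect of exercise or treatment begun after M1. The trial observes only the sum. T would need a group that continues, and there is none. N would need a record, and none is described.

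**3. What the ANOVA adds.** The arm-by-time comparison from M1 to M2 is the difference of two such sums. A cessation effect of equal size in both arms cancels out of it. It compares retention after two programmes, not stopping with continuing.

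**4. Timeline of the exercise rules.**

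| Period | Dated sentence | Undated sentence | Exercise record described |
|---|---|---|---|
| Washout, 1 week | applies | no period given | none |
| Intervention, 8 weeks | applies | no period given | supervised attendance |
| M1 to M2, 4 weeks | has ended | no period given | none |

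The dated restriction covers 1 + 8 = 9 weeks. The cessation window lies wholly outside it.

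**5. Size of the risk (illustration).** Let C = 0 and let scores drift for other reasons by δ, in SD units of the M1–M2 change. The δ values are assumptions; the document gives none. The paired t-test has noncentrality δ√n. For δ = 0.4 this is 0.4 × √15 = 1.55 in one arm and 0.4 × √30 = 2.19 pooled. The probability of a significant result (two-sided 0.05, no multiplicity adjustment) is:

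| δ | one arm, n = 15 | both arms pooled, n = 30 |
|---|---|---|
| 0 | 5% | 5% |
| 0.2 | 11% | 19% |
| 0.4 | 30% | 56% |
| 0.6 | 58% | 89% |

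**6. What can be detected.** With 80% power at two-sided 0.05, again unadjusted, the detectable M1–M2 change is 0.78 SD of the change in one arm and 0.53 SD pooled. The detectable difference in change between arms is 1.06 SD.

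**The case against.** Four counter-arguments deserve weight.

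*The objective is secondary and modestly put.* The article never promises a contrast with continued exercise, the Discussion speaks only of an effort to assess cessation, and the precedent it cites is itself a comparison with the end of the programme. A reader might infer that the objective cannot be met in any form. That goes too far: within-arm change can be described, and the randomised ALG–AG comparison at M2 is valid. What stands is that the Abstract and aims speak of an effect and an impact of stopping, which an uncontrolled change cannot show.

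*The exercise ban does not simply lapse at M1.* A reader of the dated sentence alone might conclude that it does. The undated sentence prevents that reading, so the defect is an ambiguity between two sentences.

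*Recording may be planned elsewhere.* The schedule figures are not shown, and an article may leave form-level detail to the full protocol. It would therefore be wrong to say that nothing is recorded after M1: the outcomes are measured, and the point is confined to what the text describes. The missing comparator does not depend on this.

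*The limitation is disclosed.* The Discussion admits incomplete control of outside activity and says it may act in either direction. This is to its credit, but it neither limits the cessation claim nor supplies a record.

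Two further inferences are not supported. Regression to the mean is not a main explanation of M1–M2 change: selection on VAS pain of 3 or more takes place at entry, so it acts mainly between M0 and M1. Nor does unequal resumption of exercise bias the M2 contrast when the question is persistence, because what participants do after the programmes is then part of the effect.

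**Conclusion.** The point holds in a limited form. The design cannot identify a causal effect of stopping exercise, and the text neither settles which exercise rule covers M1–M2 nor describes a record of exercise or treatment in that interval. It does support a randomised comparison of the arms at M2 and a plain description of change within each arm.

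The drift figures show how readily an uncontrolled change reaches significance. They rest on assumed drift, full data on 15 per arm and no multiplicity adjustment, and they do not estimate what will happen here. No figure can be put on how much of a cessation loss resumed exercise would hide, since the document does not say how many participants exercised beforehand or might resume.

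Because the objective is secondary and the remedy small, this should be corrected, but it does not undermine the main comparison.

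**What to change.** 1. In the Abstract, the aims and the Discussion, restate the objective as persistence of the randomised ALG–AG difference 4 weeks after the supervised programmes end, estimated as the baseline-adjusted contrast at M2.
2. Report change from M1 to M2 within each arm descriptively, without attributing it to cessation.
3. Reconcile the two sentences on other exercise in the Intervention section, so that it is clear what applied between M1 and M2.
4. At the existing M2 visit, add a short record of structured exercise, physiotherapy and analgesic use since M1, and report it by arm.

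Arms, visits, randomisation and sample size are unchanged. The cost is some rewording, one short form and a narrower claim about cessation. Data collection began in November 2024, so the form may miss M2 visits already held; the report should state how many participants it covers.

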#### Aquatic-exercise program.

This intervention will consist of an aquatic-exercise program (Table 1), administered by a physiotherapist. It will include 16 sessions, twice a week, over 8 weeks at a water temperature between 32–34 ∘ C. Each session will be conducted in groups of 8–12 patients and will last about 45 minutes. The aquatic exercise sessions will include a warm-up phase (5 minutes): walking forwards, sideways, and backwards; a training phase (35 minutes): active range of motion exercises (10 minutes) for the spine, upper and lower limbs; aerobic exercises (5 minutes) with jumps and static running at various speeds; muscle strengthening (10–15 minutes), (8–12 repetitions), 1–2 sets, 8–10 exercises including hip flexion, extension, adduction, and abduction, knee flexion and extension, knee cycling, shoulder flexion, extension, and abduction, elbow flexion, extension, and pronation-supination, squatting, and stretching exercises (5–10 minutes) for the neck, trunk, and limbs; and a relaxation/cool-down phase (5 minutes): including lying supine and low-impact exercises such as slow walking, squatting, and standing [20,37,38,41,42]. For participants who cannot complete any exercise due to difficulty or discomfort, a modified version of each exercise will be offered. The load progression will be managed using auxiliary equipment, including flotation devices, plates, balls, pull-buoys, and dumbbells, according to each participant’s RPE on the Borg CR-10 scale.

**Table 1 pone.0320858.t001:** Aquatic-exercise program.

Type	Frequency and duration	Intensity	
		Week 1–4	Week 5–8
Aquatic exercise: aerobic, resistance, and flexibility training performed in water.	2 times per week. Session duration: 40–45 min (warm-up phase: 5 min, training phase: 30–35 min; and relaxation/cool-down phase: 5 min).	Warm-up phase:	Warm-up phase:
		Low-intensity aerobic exercise: walking forwards, sideways, and backwards. RPE: 3–4 (Borg CR-10 Scale).	Low-intensity aerobic exercise: walking forwards, sideways, and backwards. RPE: 3–4 (Borg CR-10 Scale).
		Training phase:	Training phase:
		Active range of motion exercises: spine, upper and lower limbs. RPE: 3–4 (Borg CR-10 Scale).	Active range of motion exercises: spine, upper and lower limbs. RPE: 3–4 (Borg CR-10 Scale).
		Moderate-intensity aerobic exercise: jumps and static running at various speeds. RPE: 5–6 (Borg CR-10 Scale).	Moderate-to-high intensity aerobic exercise: jumps and static running at various speeds. RPE: 6–8 (Borg CR-10 Scale).
		Muscle strengthening exercises: 8–12 reps, 1 set, 8–10 exercises (hip flexion, extension, adduction, and abduction, knee flexion and extension, knee cycling, shoulder flexion, extension, and abduction, elbow flexion, extension, and pronation-supination, squatting). RPE: 5–6 (Borg CR-10 Scale).	Muscle strengthening exercises: 8–12 reps, 2 sets, 8–10 exercises (hip flexion, extension, adduction, and abduction, knee flexion and extension, knee cycling, shoulder flexion, extension, and abduction, elbow flexion, extension, and pronation-supination, squatting). RPE: 6–7 (Borg CR-10 Scale).
		Static stretching exercises: stretching for 30–45s, 1 rep, 8–10 exercises (neck, trunk, and limbs). RPE: 3–4 (Borg CR-10 Scale).	Static stretching exercises: stretching for 45–60s, 1 rep, 8–10 exercises (neck, trunk, and limbs). RPE: 3–4 (Borg CR-10 Scale).
		Relaxation/cool-down phase:	Relaxation/cool-down phase:
		Low-intensity exercise: slow walking, squatting and standing. RPE: 2–4 (Borg CR-10 Scale).	Low-intensity exercise: slow walking, squatting and standing. RPE: 2–4 (Borg CR-10 Scale).
		Diaphragmatic breathing/ Floating. RPE: 0–2 (Borg CR-10 Scale).	Diaphragmatic breathing/ Floating. RPE: 0–2 (Borg CR-10 Scale).

Notes: min, minutes; RPE, rate of perceived exertion; reps, repetitions; s, seconds.

#### Land-exercise program.

This program will include specific land-based exercises (Table 2, guided by a physiotherapist. This intervention will include 8 sessions in 8 weeks, once a week, on a different day from the aquatic exercise program. Each session will last between 25 to 35 minutes and will be divided into two components: core stability exercises and stretching of the trunk and lower limbs [60]. Core stability exercises (15–20 minutes): these will consist of isometric exercises which contraction was maintained for 7–8 seconds, 8–12 repetitions, 1 set, with brief rest intervals of 3 seconds between repetitions and 30 seconds to 1 minute between exercises [60,61]. Exercises will include abdominal hollowing, side bridge (both sides), supine extension bridge, lower limb extension from prone (both sides), and alternate arm and leg raise from quadruped. Intensity will increase gradually by reducing rest time between exercises and increasing repetitions, based on participants’ performance. Participants will be instructed to contract and hold their abdominal muscles while maintaining normal breathing patterns [62]. Stretching exercises (10–15 minutes): participants will perform muscle stretching exercises, holding the maximum stretch for 30 seconds to 1 minute, and returning to the original position, followed by 5–10 seconds of rest. Each exercise will be repeated two to three times [63]. Stretches will target the hamstrings, iliopsoas, piriformis, and tensor fasciae latae. Participants will be instructed to minimize tension in other body muscles and maintain their usual breathing pattern during stretching [64–67].

**Table 2 pone.0320858.t002:** Land-exercise program

Type	Frequency and duration	Intensity	
		Week 1–4	Week 5–8
**Core stability exercises:** abdominal hollowing, side bridge (both sides), supine extension bridge, lower limb extension from prone (both sides), and alternate arm and leg raise from quadruped, performed in dry land.	1 time per week. Session duration: 25–35 min	**Isometric strength exercises:** contraction held for 7–8s, 8–10 reps, 1 set.	**Isometric strength exercises:** Contraction held for 9–10s, 10–12 reps, 1 set.
	(Core stability exercises: 15–20 min, and stretching exercises: 10–15 min).	Rest between reps: 3s	Rest between reps: 3s
		Rest between exercises: 1min.	Rest between exercises: 30s.
		RPE: 5–6 (Borg CR-10 Scale)	RPE: 6–7 (Borg CR-10 Scale)
**Stretching exercises:** stretching the hamstrings, iliopsoas, piriformis, and tensor fasciae latae, performed in dry land.		**Static stretching exercises:** stretching for 30–45s.	**Static stretching exercises:** stretching for 45–60s.
		2 reps.	3 reps.
		Rest between reps: 5–10s.	Rest between reps: 5–10s.
		RPE: 5–6 (Borg CR-10 Scale)	RPE: 5–6 (Borg CR-10 Scale)

Notes: min, minutes; s, seconds; reps, repetitions; RPE, rate of perceived exertion.

